**Figure 2 Fig2:**
[figure not shown]
**Location of facial acupoints.** Four points are used for adolescents in the acupuncture group which includes bilateral Cuanzhu (BL2), Tongziliao (GB1), Sibai (ST2), and Muchuang (GB16).

**Figure 3 Fig3:**
[figure not shown]
**Location of hand acupoint.** Bilateral Hegu (LI4) is used for adolescents in the acupuncture group.

### Data collection

Baseline data will be collected before the first treatment. The information collected will include gender, date of birth, ethnicity, height, birth weight, current body weight, premature or full-term baby, parental myopia, sibling myopia, time of reading at a close distance, time of daily outdoor activities, performance of daily eye exercises, room lighting, and bad reading habits (reading while lying, walking, or riding on the bus).

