**Methods/Design:**

A randomized, parallel, single-center, assessor- and statistician-blinded, controlled clinical trial will be performed. A total of 100 teenagers, between seven and 12 years of age, with mild-to-moderate myopia and spherical lenses <-6.00 D and cylindrical lenses <-1.50 D will be selected from the Xinjiang Uygur Autonomous Region Institute of Traditional Chinese Medicine, a grade III level A teaching hospital in Urumqi, Xinjiang, China (Xinjiang Medical University Affiliated Hospital of Traditional Medicine). The subjects will be randomly assigned to two different groups (control and acupuncture groups), each group containing 50 subjects. The subjects in both groups wear single-vision corrective lenses. In the acupuncture group, acupuncture will be performed daily for nine consecutive days on five points (bilateral Cuanzhu, Tongziliao, Sibai, Muchuang, and Hegu), followed by no treatment for one day. Six cycles of treatment will be undertaken continuously for a total of 60 days. Following 60 days of treatment, a follow-up period of six months will be included. The primary outcome will be diopter determination. The secondary outcomes will include distance visual acuity, axial length, lens thickness, ciliary body thickness, and subjective symptoms of the eyes and entire body. The main time points for the evaluation of clinical efficacy will be the first, third, and sixth months after treatment.

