**Table 1 Tab1:** **Time of visit and data collection**

Data obtained/recorded	Baseline	Treatment phase	Visit 1	Visit 2	Visit 3
	-7 days	1-2 months	3 months	5 months	8 months
Signed informed consent	×				
Medical history	×				
Met the diagnostic standard/exclusion criteria	×				
General record	×				
Diagnosis	×				
Visual acuity	×		×	×	×
Diopter	×		×	×	×
Axial length	×		×	×	×
Lens thickness	×		×	×	×
Ciliary body thickness	×		×	×	×
Skin damage	×	×	×	×	×
Eye symptoms and systemic symptoms	×	×	×	×	×
Randomization	×				
Group therapy	×				
Case report form	×		×	×	×
Adverse event		×	×	×	×
Close-out					×

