### Recruitment strategies

The subjects will be informed of the details regarding the trial plan and those who voluntarily participate in the trial will receive free ophthalmologic examinations. Following optometric evaluation, these subjects will receive the highest discount (30% off) on glasses. Subjects in the experimental group will receive a 50% discount on acupuncture treatment. All subjects who receive a follow-up eye exam will not pay a fee and will be permitted to be fast-tracked. The subjects who will be included in the experimental group will receive treatment any time between 10:00 and 19:00 (Beijing time). If adverse events occur during treatment, the treatment will be immediately terminated, and help will be obtained from the emergency department. According to the specific condition which occurs after treatment, a consultation involving at least three experts will be carried out to decide whether or not to continue the clinical trial. Subject compliance will be determined based on whether or not the subject receives due treatment. The researchers will ensure that the subjects in the experimental group fully understand the importance of regular acupuncture and compliance. During the observation period, the use of drugs or other therapies to treat mild-to-moderate myopia will be prohibited.

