### Intervention

Subjects in the acupuncture group will wear SVLs. Acupuncture will be performed at five acupuncture points (bilateral Cuanzhu (BL2), Tongziliao (GB1), Sibai (ST2), Muchuang (GB16), and Hegu (LI4), see Figures 
2 and
3). Alcohol (75%) will be used to routinely disinfect the local skin at the acupuncture points and 0.25 mm × 0.4 mm disposable sterile acupuncture needles (Suzhou Acupuncture & Moxibustion Appliance Co., Ltd., Suzhou, China) will be used at acupuncture points Sibai and Hegu to a depth of 0.5 to 1.0 cm. After achieving *de-qi* (Subjects have a feeling of soreness, fullness, aching, heaviness at and around the acupoints), the needle will be held in position for 20 minutes. Cuanzhu will be acupunctured to a depth of 0.3 to 0.5 cm. Tongziliao and Muchuang will be acupunctured to a depth of 0.1 to 0.3 cm. After achieving *de-qi*, the needle will be held in position for 20 minutes. Acupuncture will be carried out once a day between 10:00 and 19:00 (Beijing time). One cycle of treatment will last for nine days, followed by one day of no treatment. Six cycles of treatment will be undertaken continuously for a total of 60 days. The acupuncturist in this study, a physician with 18 years of experience in clinical acupuncture, will not participate in objective examinations, such as visual acuity. Subjects in the control group will wear SVLs without any other treatment affecting visual acuity. Observations will be carried out for two consecutive months.

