**Table 2 Tab2:** **Variables, measures, and methods of analysis**

Variable/outcome	Hypothesis	Outcome measure	Methods of analysis
1) Primary	Intervention improved outcome from baseline to 7 days	Adherence% (>80%) [binary]	
Diopter	Diopter reduced or increased after treatment	Diopter [continuous]	t-test (rank-sum test) or repeated measurement
2) Secondary	Intervention improved outcome from baseline to 7 days	Adherence% (>80%) [binary]	
Visual acuity	Visual acuity did not increase or decrease after treatment	Visual acuity changes [continuous]	t-test (rank-sum test) or repeated measurement
Axial length	Axial length was not increased	Axial length changes [continuous]	t-test (rank-sum test) or repeated measurement
Lens thickness	Lens thickness was not increased	Lens thickness changes [continuous]	t-test (rank-sum test) or repeated measurement
Ciliary body thickness	Ciliary body thickness was not increased	Ciliary body thickness changes [continuous]	t-test (rank-sum test) or repeated measurement
Eye symptoms and systemic symptoms	No adverse symptoms	No adverse symptoms	Chi-squared test or Fisher’s exact test
Compliance	Compliance	Cure rate [binary]	Chi-squared test or Fisher’s exact test
Combination therapy/treatment	Improvement occurred	Whether other drugs were used during treatment [binary]	Chi-squared test or Fisher’s exact test
Adverse event	Improvement occurred	Presence of drug-related adverse event [binary]	Chi-squared test or Fisher’s exact test
3) Baseline analyses:		Adherence% (>80%) [continuous]	
Age		CRF [continuous]	t-test (rank-sum test)
Weight and height		CRF [continuous]	t-test (rank-sum test)
Female versus male		CRF [binary]	Chi-squared test or Fisher’s exact test
Race		CRF [more categories]	Chi-squared test or rank-sum test
Birth weight		CRF [continuous]	t-test (rank-sum test)
Preterm children		CRF [binary]	Chi-squared test or Fisher’s exact test
Parental myopia or not		CRF [binary]	Chi-squared test or Fisher’s exact test
Sibling myopia or not		CRF [binary]	Chi-squared test or Fisher’s exact test
Daily close reading time		CRF [continuous]	t-test (rank-sum test)
Outdoor time		CRF [continuous]	t-test (rank-sum test)
Eye exercises every day or not		CRF [binary]	Chi-squared test or Fisher’s exact test
Daily sleep time		CRF [continuous]	t-test (rank-sum test)
Room light conditions		CRF [binary]	Chi-squared test or Fisher’s exact test
Poor reading habits		CRF [more categories]	Chi-squared test or rank-sum test

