The limitations of the proposed study are three-fold. Firstly, due to a limited budget, the proposed study will not be a multicenter trial, which will influence the external validity of the conclusions. Secondly, common fake acupuncture methods include neighboring sham acupuncture, non-specific site acupuncture, superficial acupuncture, minimal acupuncture, and a placebo needle; all of these methods could be used as a control, but with obvious deficiencies
[33]. Therefore, in the proposed study a sham acupuncture group will not be included. Quantitative, objective indices, such as diopter, AL, lens thickness, and ciliary body thickness will be selected as the outcomes to evaluate the clinical efficacy at a reduced bias. Thirdly, in the proposed study, 100 cases will be included and followed up on for six months. To prevent bias caused by loss-to-follow-up, the following measures will be adopted: first, the subjects will be from an elementary school near the hospital. Second, before the subjects are entered into the proposed study, their guardians will fully understood the specific requirements of the follow-up schedule, as outlined in the informed consent form. Once the subjects are included in the study, communication with the guardians will be strengthened by phone calls or email. The subjects will be informed of the follow-up examination time and place in advance. The subjects will receive the follow-up examination immediately after arriving.

This will be a randomized, parallel controlled trial, and it is anticipated that acupuncture treatment of adolescent mild-to-moderate myopia will be shown to be safe and effective. The proposed study will demonstrate the specificity of the meridians and acupuncture points and provide evidence-based medical evidence on the use of acupuncture to treat myopia.

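### Reading, outdoor and eye-exercise habits are scheduled at baseline only and no lens-wear measure is named, so the trial can support an effect of attendance plus needling but not of needling itself

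*Protocol article*

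**What the plan says.** **Habits.** Under Data collection, "Baseline data will be collected before the first treatment", and the items listed include "time of reading at a close distance, time of daily outdoor activities, performance of daily eye exercises, room lighting, and bad reading habits". In Table 1 the row "General record" is marked at baseline only. The rows marked at visits 1 to 3 cover the ocular measures, skin damage, symptoms, the case report form and adverse events. Table 2 places "Daily close reading time" and the other habit variables in its block of baseline analyses.

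**Lens wear.** According to the Abstract, "The subjects in both groups wear single-vision corrective lenses". Under Intervention, "Subjects in the control group will wear SVLs without any other treatment affecting visual acuity". Neither the text nor the tables name a measure of how much the lenses are worn.

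**Contact and compliance.** Under Intervention, acupuncture is given daily for nine days out of ten over six cycles. Recruitment strategies defines compliance by receipt of the treatment due, and adds: "The researchers will ensure that the subjects in the experimental group fully understand the importance of regular acupuncture and compliance". The same section bans drugs and other therapies for myopia but does not mention habits.

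**Handling of bias and the claim made.** The Discussion explains that there is no sham arm and says that objective indices "will be selected as the outcomes to evaluate the clinical efficacy at a reduced bias". It then expects the trial to demonstrate that meridians and acupuncture points are specific.

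**The concern.** By collecting the habit items, the plan treats them as relevant to myopia. After randomisation the arms differ in more than needling: one attends a clinic almost daily for two months and is counselled on compliance, the other wears lenses and is observed. Families know which arm they are in.

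Objective instruments and blinded assessors guard against biased measurement. They do not guard against a real change in refraction or axial length that arises because children in one arm came to read, play outdoors or wear their lenses differently. Comparing the arms at baseline cannot reveal a change that happens later.

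What is at stake is the interpretation of a positive result. A dioptre difference could contain a behavioural component, and the data described give no means of seeing whether it does.

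**Working it through.** **1. Schedule, source by source**

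| Source (Protocol article) | Habit items | Lens wear |
|---|---|---|
| Data collection | Listed, before first treatment | Not listed |
| Table 1 | No follow-up row; general record at baseline only | No row |
| Table 2 | Baseline analyses only | Not named; Adherence and Compliance rows undefined |
| Recruitment strategies | Not mentioned | Compliance means receipt of due treatment |

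The first three sources agree that habits are baseline data. For lens wear the article is silent rather than explicit.

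**2. Contact during treatment**

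Six cycles × 9 treatment days = 54 acupuncture sessions in 60 days, against none for controls. This contrast is documented for the treatment phase only, not for the six-month follow-up.

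**3. How large an unmeasured difference would matter**

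The plan gives no figure for a habit effect, so there is none to reproduce. The calculation below is an illustration.

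Inputs from Sample size and Statistical analysis: SD 0.25 D; one-sided α = 0.05; 50 per arm, or 50 × 0.8 = 40 per arm after the planned 20% dropout; boundary 0.2 D. Assumed: no needling effect, and a non-needling difference *b* of 0.05 or 0.10 D in favour of acupuncture.

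- Standard error = 0.25 × √(2/n): 0.0500 D at n = 50 and 0.0559 D at n = 40.
- Smallest significant observed difference against zero = t(0.95; 2n − 2) × SE: 1.661 × 0.0500 = 0.083 D, and 1.665 × 0.0559 = 0.093 D.
- Probability of a significant result = upper tail of the noncentral t distribution with 2n − 2 degrees of freedom and noncentrality *b*/SE for a test against zero, or (*b* − 0.2)/SE for a test against the boundary.

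| *b* | n per arm | Test against zero | Test against 0.2 D |
|---|---|---|---|
| 0.05 D | 50 | 25.7% | 0.0002% |
| 0.05 D | 40 | 22.4% | 0.0008% |
| 0.10 D | 50 | 63.4% | 0.014% |
| 0.10 D | 40 | 55.1% | 0.032% |

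**4. Which column applies**

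The sample-size section uses the 0.2 D boundary. The analysis section speaks of a superiority test, and Table 2 names a t-test, rank-sum test or repeated-measures analysis; neither restates the boundary. Both columns are therefore possible readings. Under the second, a bias of this size would almost never produce a positive result by itself, but it would still be added in full to the estimated difference.

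**The case against.** The case on the other side has five parts.

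- **The mechanism is conjecture.** The counselling is about acupuncture and compliance, not reading, outdoor time or lenses, and nothing says that the acupuncturist gives habit advice. Clinic time could displace outdoor time as easily as near work, so even the direction is unknown. Controls also have some contact: Table 1 schedules symptom and adverse-event checks during treatment without separating the arms, and the Discussion promises calls or emails to guardians. All of this stands. A reader might infer that habits will diverge, or that such a change would be credited to needling. The documents support only that it could happen unseen.
- **Lens wear may be recorded after all.** The case report form is not shown. Table 2 includes daily sleep time, which the Data collection list omits, so that list is not complete. The controls' only treatment is lenses, and the Compliance row has a between-group test, so it might cover lens wear. This stands against any reading that lens wear is never recorded. It does not show that it is: the Adherence rows are undefined, and the Compliance row gives a cure rate as its measure.
- **The false-positive figures depend on the test.** Quoting only the test against zero would mislead, since the 0.2 D boundary makes a false positive from biases of this size negligible. This stands, which is why both are shown.
- **The randomised contrast is valid.** Behaviour change caused by assignment is part of the effect of assignment. This is correct, and a reader should not infer that the comparison itself is invalid. The difficulty is the narrower claim about needling and specific points.
- **Recording habits does not cure the absence of a sham,** which the article already discloses. This is correct. Unmasked self-report is itself open to differential reporting and cannot separate needling from attention.

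**Conclusion.** The point holds in a limited form, as an optional improvement. The habit items are fixed as baseline-only consistently in the text and both tables, and the article names no lens-wear measure. With families unmasked and contact unequal in the treatment phase, a differential change is plausible but not shown, and the data described could not detect it. The trial can estimate the effect of attendance plus needling. It cannot support the Discussion's claim about the specificity of meridians and points.

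The size of any bias is unknown. The illustrative 22–26% (0.05 D) and 55–63% (0.10 D) rest on assumed bias sizes, SD 0.25 D, 40 to 50 per arm, no needling effect and a one-sided test against zero. With the 0.2 D boundary enforced they fall below 0.1%, and the consequence for biases of this size is an inflated estimate rather than a false claim of superiority.

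**What to change.** 1. In Table 1, add rows at visits 1 to 3, in both arms, for the habit items already asked at baseline and for one question on daily lens wear. If the Adherence or Compliance row is meant to cover lens wear, say so and define it.
2. Give both arms the same scripted habit and lens-wear advice at baseline, with its content left to the investigators.
3. Report these items descriptively by arm beside the primary result. Label any adjusted analysis exploratory, because the items are measured after randomisation.
4. Word the conclusion as the effect of the attendance-plus-needling package whatever the habit data show, and drop the claim of point specificity.

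The cost is a few minutes of questionnaire at three visits already scheduled, the added table rows and a short script. The Trial status section reports six participants recruited, so at that date nearly all follow-up could still be covered. The limitation is that the data are unmasked self-report: they are supportive only and do not replace a sham control, and equal advice at baseline does not equalise contact.

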### Primary outcome

The primary outcome in this trial will be diopter measurement
[21]. After mydriasis using cyclopentolate hydrochloride eye drops (15 ml; Alcon-Couvreur, Puurs, Belgium), a comprehensive refractometer (AOS-1,500; Nidek, Aichi, Japan) will be used to conduct objective optometry (computer optometry and retinoscopy), then subjective optometrics. Subjective optometrics will be divided into the following two parts: optometrics will be conducted on a single eye (the right eye followed by the left eye), and a bilateral eye balance examination. Subjective optometrics of a single eye will be divided into the following three stages: the initial maximum plus the maximum visual acuity (MPMVA) will be identified, Jackson cross cylindrical lenses will be used to determine the axial direction and degree of the cylindrical lens, and the MPMVA will be repeated. The results will be recorded after optometrics. When the pupils recover, a re-examination will be carried out (three days after the use of cyclopentolate hydrochloride eye drops). After re-examination, the glasses will be tried again. The degree of the glasses will be marked on the glass trial frame, to be chosen by the subjects based on subjective judgment. Finally, the diopter of the glasses and prescription glasses will be determined. The optometrist will not participate in other parts of the trial. The main time points for evaluation of clinical efficacy will be the first, third, and sixth months after two months of treatment.

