### Statistical analysis

All statistical analyses will be performed using SPSS 17.0 statistics software. For quantitative data, the distribution pattern and homogeneity of variance will be examined. If there is a symmetric distribution, the mean (M) ± standard deviation will be used for statistical description, otherwise the M interquartile range (IQR) will be used to describe the trend of concentration and amount of scatter. If this condition is met, the Student's t-test will be used to compare the differences between the quantitative indices between the groups, otherwise the Wilcoxon rank-sum test will be used. For categorical data (binary classification and multiple classification), the composition ratio will be used for statistical description. Based on the observation of a theoretical frequency distribution, the χ^2^ or Fisher's exact test will be used, depending on the specific situation. The ranked data will be analyzed using the Wilcoxon rank-sum test.

Primary and secondary outcomes will be analyzed by the superiority test in accordance with the principle of intention-to-treat, using Per Protocol Set (PPS) and Full Analysis Set (FAS) datasets. The indices of safety evaluation will be analyzed using the Save Set (SS) dataset. The significance level in this study will be set at α = 0.05, and the one-sided test will be used. The detailed statistical analytical methods for primary and secondary outcomes and baseline data are shown in Table 
2 (variables, measures, and methods of analysis).

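### The plan relies on diopter as an objective index, but its primary-outcome procedure is partly subjective and no section says which reading is analysed

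*Protocol article*

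**What the plan says.** The Primary outcome section opens with "The primary outcome in this trial will be diopter measurement". The refractometer is then used, after cyclopentolate, "to conduct objective optometry (computer optometry and retinoscopy), then subjective optometrics". The subjective part has two components: "optometrics will be conducted on a single eye (the right eye followed by the left eye), and a bilateral eye balance examination". Results are recorded once this refraction is done. About three days later, when the pupils have recovered, the child is re-examined and tries lenses again, with the power of the trial frame "to be chosen by the subjects based on subjective judgment". The description of the measurement ends: "Finally, the diopter of the glasses and prescription glasses will be determined".

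In the Discussion, the limitation about sham control is followed by this assurance: "Quantitative, objective indices, such as diopter, AL, lens thickness, and ciliary body thickness will be selected as the outcomes". The stated purpose is to evaluate efficacy with less bias.

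Under Statistical analysis, if the distributional conditions are met, "the Student's t-test will be used to compare the differences between the quantitative indices between the groups"; otherwise the rank-sum test is used. Table 2 lists the primary variable only as a continuous diopter, analysed by t-test, rank-sum test or repeated measurement. Study design describes blinding of the assessor and the statistician. Under Intervention, the control children wear single-vision lenses and receive no needling.

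**The concern.** The children cannot be blinded: one arm is needled in nine-day daily cycles over 60 days and the other only wears lenses. In that setting an outcome is protected against the child's expectation only if it does not depend on the child's answers. The plan claims this protection for diopter, yet most steps of its diopter procedure ask the child to respond or choose.

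Two things are at stake. If a response-dependent reading is analysed, part of any difference between arms may reflect expectation. And because several readings per visit could each be called the diopter, the primary variable could be settled after the data have been seen.

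**Working it through.** The plan gives no figure on this point to reproduce. The check sets the sections side by side and then illustrates size under stated assumptions.

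**Step 1. Candidate values per visit (Primary outcome section).**

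| Step | Reading | Depends on the child's answers? |
|---|---|---|
| 1 | Computer refraction after cyclopentolate | No |
| 2 | Retinoscopy | No (examiner's judgement) |
| 3 | Subjective refraction, right eye then left | Yes |
| 4 | Binocular balance | Yes |
| 5 | Re-examination about three days later | Method not stated |
| 6 | Trial-frame power | Yes (child's choice) |

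The sentence on recording results stands between steps 4 and 5 and does not say which reading it covers. The sentence that a diopter is finally determined stands after step 6 and refers to the glasses. Table 2 does not choose among the readings and gives no rule for combining sphere and cylinder.

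**Step 2. Who is blinded.** The assessor and statistician are (Study design, Implementation), and the optometrist takes no other part in the trial (Primary outcome). This limits examiner bias in steps 1 to 6. It does not act on the child's own answers in steps 3, 4 and 6.

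**Step 3. Illustration of size.** The SD of 0.25 is taken from the Sample size section. There are 50 children per arm, or 40 after the planned 20% dropout. The bias *b* is an **assumption**; the documents give none.

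- SE = 0.25 × √(2/n) = 0.050 D for n = 50 and 0.056 D for n = 40.
- Chance of a false positive in a one-sided 5% test against zero difference = 1 − Φ(1.645 − b/SE).

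| Assumed b | n = 40 per arm | n = 50 per arm |
|---|---|---|
| 0 | 5% | 5% |
| 0.05 D | 23% | 26% |
| 0.10 D | 56% | 64% |

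These figures show how sensitive the test is at this sample size. They do not estimate the bias in this trial. They also apply to a test against zero, not against the 0.2 margin in the Sample size section.

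**Step 4. Supporting check on eyes.** Children are randomised, both eyes are refracted, and the t-test and rank-sum test need independent values. *If* both eyes were entered as independent, with between-eye correlation ρ (an **assumption**; none is given), the variance of each arm mean would be understated by a factor of 1 + ρ:

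- true one-sided error = 1 − Φ(1.645/√(1+ρ));
- true two-sided error = 2[1 − Φ(1.96/√(1+ρ))].

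| ρ | One-sided 5% test | Two-sided 5% test | Effective value of 100 eyes per arm |
|---|---|---|---|
| 0.5 | 9.0% | 11.0% | 67 |
| 0.8 | 11.0% | 14.4% | 56 |
| 0.9 | 11.6% | 15.5% | 53 |
| 0.95 | 11.9% | 16.0% | 51 |

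Both test directions are shown because the Sample size section calls α two-sided, while Statistical analysis specifies a one-sided test.

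**The case against.** The strongest reply is that the child's choice concerns spectacles. It comes after the pupils have recovered and after results have been recorded, and it leads to a prescription. The Recruitment section defines eligibility by refraction under cycloplegia, so a reader may reasonably assume that the outcome is also the cycloplegic result. This stands to the extent that a reader might infer that the child-chosen power is the primary endpoint, and no section says so. It does not close the point: the recorded cycloplegic result may itself be the subjective refraction, and no section names the objective reading.

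A reader might also infer that sham was dropped because diopter is objective. The Discussion gives another reason, the shortcomings of the available sham methods, and offers objective indices as mitigation. Nor are they the only safeguard, since assessor and statistician blinding are others. The description as objective is not disputed here for axial length, lens thickness or ciliary body thickness, or for the first two refraction steps.

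On eyes, a rule may stand in a fuller plan that is not shown. The article counts 100 subjects and nowhere says that eyes will be treated as independent, so the error rates in Step 4 describe an analysis that it does not state. Table 2 also allows a repeated-measurement analysis.

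Finally, neither the size nor the direction of any response bias is known. The maximum-plus procedure has a set endpoint, and a child may not know which answer implies less myopia. That is a fair limit on the illustration in Step 3.

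**Conclusion.** The point holds as an inconsistency within the article. Diopter is relied on as objective to limit bias in a trial without sham, but the procedure under the primary-outcome heading moves from objective to subjective readings, and the analysed reading is not named. Any reading after the objective steps that uses the child's answers is exposed to a bias that assessor blinding does not remove. The documents give no size for it. Under the plan's SD, a systematic shift of 0.05 D would equal 0.9 to 1.0 standard errors, so even a small bias could matter.

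The documents do not support saying that the child's lens choice is the analysed outcome, or that the test will run at 11% to 16% error. That range needs both eyes entered as independent and an assumed correlation of 0.8 to 0.9. The missing rule for one value per child is a supporting point only.

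**What to change.** State in the Primary outcome section and in Table 2 that the primary variable is the cycloplegic computer refraction, expressed as spherical equivalent (sphere plus half the cylinder) and recorded before any subjective step. Report subjective refraction as a secondary outcome. Retinoscopy would also come before the child's answers; computer refraction is suggested because it depends less on the examiner. The case report form should hold the objective reading in its own field.

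In the same sentence, define one value per child, for example the mean of the eyes that qualify at baseline. Averaging both eyes regardless could bring in an eye that does not meet the refractive limits. The article states the right-then-left order only for the subjective step, so it should confirm that computer refraction is taken in each eye that counts.

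No new measurement is needed if the described procedure is followed at baseline and at the three follow-up visits, as Table 1 implies. The cost is that subjective refraction becomes secondary and that the change must be notified to the Ethics Committee, subjects, register and publisher, as the amendments section requires. Trial status reports six children already recruited, so it should be checked that their objective readings were kept.
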